#### Instrumental variable analysis

In our third analysis, we will estimate the effects: (1) treatment or no treatment and (2) the specific subclass of medication prescribed, using physicians' prescribing preferences as instruments for the prescriptions the GPs issue to their patients. We cannot directly measure the physicians' preferences; therefore, we will use the prescriptions they issued to their previous patients as a proxy for their preferences. For example, if the instrument were based on just one previous prescription, physicians who previously prescribed the treatment therapy would be categorised as a ‘treatment prescriber’ otherwise they would be categorised as a ‘control prescriber’. As with our previous studies we will use seven prior prescriptions to improve the strength of the instruments.^25–27^ Using multiple prior prescriptions will maximise power. We will report risk differences in the outcomes using additive structural mean models estimated via the generalised method of moments.^28–30^ We will categorise each of the adverse event outcomes as occurring within 3, 6, 9, 12, 24 and 48 months of index date. Methods for estimating survival models using instrumental variables are not well developed. Therefore, we will explore potential instrumental variable survival models in a secondary analysis.^31^

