**Figure 1 BMJOPEN2016012044F1:**
[figure not shown]
The cohort construction for cohort type A, designed to eliminate immortal time bias. A patient will enter the cohort for a given treatment when they first become ‘at risk’ of the condition the treatment is used for or, in the case of no period ‘at risk’, when they are first diagnosed with the condition (see table 2). For example, when they are diagnosed as at ‘at risk of’ hypertension or, in the case of no period ‘at risk’, when they receive a diagnosis of hypertension. We define cohort entry in this way to avoid excluded immortal time bias that can occur when cohort entry is determined by treatment variation over time.^33^
^34^ Immortal time is the period during follow-up when the outcome cannot occur. Consider the hypertension example above, suppose we started following the treated patients in our cohort from the date of their first prescription of a treatment for hypertension and the untreated patients from a matched date. This would make it impossible for the treated patients to have an outcome, such as dementia, prior to their first prescription. Consequently, patients in this group would all have a period before treatment, when they could not be diagnosed with dementia, that is, they could not experience the outcome. This period is their immortal time, and it must be correctly attributed to the ‘unexposed’ group so that their outcome is not falsely attributed to their exposure. To do this, patients in the ‘exposed’ and ‘unexposed’ groups must be followed-up and compared from the same start date. In this cohort, we are minimising excluded immortal time by following patients from either a test result or diagnosis where possible. In order to capture all relevant patients, we will allow those receiving treatment without a recorded diagnosis to be included as it is assumed treatment suggests a diagnosis.

10.1136/bmjopen-2016-012044.supp1supplementary file

10.1136/bmjopen-2016-012044.supp2supplementary file

10.1136/bmjopen-2016-012044.supp3supplementary file

Follow-up for cohort A will start on the first date a patient is diagnosed with the condition the treatment is used for or ‘at risk’ of that condition (see table 2 and online supplementary files 1–3.) Follow-up will end with the earliest of a relevant neurodegenerative disease diagnosis, death or censoring due to the end of registration at a CPRD general practice.

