### Confounding

We have identified two key sources of confounding in our study: confounding by indication and time-dependent confounding. To address the former, we will use four different statistical methods, which have different approaches for modelling confounding. Through examination of these approaches, we hope to highlight any uncontrolled confounding that may be leading to false conclusions about drug effect. We will also account for confounding by indication in the construction of our cohorts. Consider cohort A, where we compare ‘exposed’ and ‘unexposed’ groups of individuals. Drawing the ‘unexposed’ group from the full population can introduce bias as they are likely to be in better health. We will avoid this by defining cohort entry on the basis of first test or recording of a relevant read code so the ‘exposed’ and ‘unexposed’ groups will have more in common. In addition to this, we will address time-dependent confounding in our study. This will be carried out using marginal structural models, which can allow for time-dependent confounding and treatment switching between products.

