#### Multivariable adjusted Cox regression

In our first analyses, a conventional observational analysis, we will estimate the HRs of incidence and survival using Cox proportional hazards models. Both analyses will use the actual prescriptions issued to the patients.^20^ We will report these associations adjusted for basic confounders (age and gender) and results adjusted for all measured covariates described previously. We will also perform tests of the proportional hazards assumption.

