#### Propensity matched regression

In our second analysis, we will construct a sample of patients balanced on covariates and risk factors using a propensity score.^21–24^ We will construct propensity scores using a logistic regression of the actual treatment received on the covariates described above. Therefore, each participant's propensity score will be their conditional probability (odds) of receiving treatment or not (cohort types A and C), or receiving treatment versus control therapy (cohort type B). We will match each patient receiving one treatment to another patient receiving the control treatment with the closest propensity score on a ratio of 1:1 using a nearest neighbour algorithm with no replacement, and matching will be restricted to the common support region. Patients outside the common support region are those prescribed the treatment therapy with propensity scores higher than any patient prescribed the control treatment and vice versa. We will estimate odds ratios and HRs of the outcomes using the propensity score matched sample using logistic and Cox regressions.

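### The main instrumental variable analysis gives risk differences only to 48 months, so the size of any disagreement with all-follow-up Cox hazard ratios is hard to attribute to confounding

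*Protocol article*

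**What the plan says.** The Instrumental variable analysis section fixes the effect measure: "We will report risk differences in the outcomes using additive structural mean models estimated via the generalised method of moments". It fixes the timing in the next sentence: "We will categorise each of the adverse event outcomes as occurring within 3, 6, 9, 12, 24 and 48 months of index date". The phrase about adverse events does not match the outcomes the study defines, which for incidence are the four neurodegenerative diseases; I take it to mean those. The section then says that "Methods for estimating survival models using instrumental variables are not well developed" and that "we will explore potential instrumental variable survival models in a secondary analysis". Table 1 lists IV for cohorts A and B but not for cohort C.

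For the conventional analysis, "we will estimate the HRs of incidence and survival using Cox proportional hazards models". Follow-up in cohorts A and B has no fixed horizon: "Follow-up will end with the earliest of a relevant neurodegenerative disease diagnosis, death or censoring" at the end of practice registration. In cohort A it starts at the at-risk date where there is one (Table 1), while exposure is defined by treatment within 6 months of the diagnosis (Cohort A section).

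On the purpose of using several methods, the Confounding section says that by examining them "we hope to highlight any uncontrolled confounding that may be leading to false conclusions about drug effect". The Covariates section names IV as a way to reduce confounding from unrecorded variables. The Statistical methods section leaves discrepancies to a judgement on each method's merits.

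The Propensity matched regression section adds odds ratios: "We will estimate odds ratios and HRs of the outcomes using the propensity score matched sample using logistic and Cox regressions". The Marginal structural models section also plans odds. Neither states a time window for them.

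**The concern.** If comparing methods is to reveal confounding, the methods should target the same quantity, or be convertible to it, so that a difference points to the assumptions about confounding. Here the main IV result differs from the Cox result in three other ways.

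- **Horizon.** IV looks at no more than the first 48 months; Cox uses everything. The diseases develop slowly. If a drug's effect appeared only after 48 months, all six IV risk differences would be zero while the Cox hazard ratio was not, with no confounding anywhere.
- **Scale.** A risk difference depends on baseline risk and elapsed time. A hazard ratio does not convert to it without both.
- **Clock in cohort A.** The windows run from the at-risk date, not from treatment, so the early ones may contain no treated time for some exposed patients.

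At stake is the reading of the study's own check on unmeasured confounding. A gap in size between IV and Cox could be taken as evidence of confounding when it reflects horizon or scale, or a real confounding difference could be dismissed on the same ground.

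**Working it through.** The protocol states no event rate, follow-up length or IV power, so there is no figure of its own to reproduce. Every hazard and follow-up length below is an assumption.

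**1. Share of observed events inside 48 months.** Let follow-up be uniformly censored up to F years, with event hazard h(t) and event-free survival S(t). The share is

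∫₀⁴ h(t)S(t)(1 − t/F) dt ÷ ∫₀^F h(t)S(t)(1 − t/F) dt.

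| Assumed hazard | F = 15 years | F = 20 years |
|---|---|---|
| 0.003/year, doubling every 5 years | 0.0136/0.0491 = 28% | 0.0142/0.0876 = 16% |
| constant 0.005/year | 0.0172/0.0366 = 47% | 0.0178/0.0484 = 37% |

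The range is 16% to 47%. Adding a 10%/year exit rate to the doubling hazard gives 42% and 31%, inside that range.

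**2. One true effect, several risk differences.** Take a constant control hazard of 0.005/year, a true hazard ratio of 0.8, no confounding and no censoring. The risk difference at T is exp(−0.005T) − exp(−0.004T).

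- T = 4 years: −3.9 per 1,000
- T = 10 years: −9.6 per 1,000
- T = 15 years: −14.0 per 1,000

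Cox reports 0.8 throughout, while the risk difference at 15 years is about 3.6 times that at 4 years (14.0/3.9). At T = 4 years the same hazard ratio gives −1.6 per 1,000 with a control hazard of 0.002/year and −7.7 with 0.01/year. Without Cox-based risks at the IV horizons, a reader cannot tell whether an IV estimate agrees in size with the hazard ratio.

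**3. Cohort A clock.** Suppose diagnosis comes d months after the at-risk date and treatment follows diagnosis within the permitted 6 months. Treatment then starts between d and d + 6 months after index. If d exceeds 12, the 3-, 6-, 9- and 12-month windows have all closed before treatment. The protocol does not say how often this happens. It cannot arise in cohort B, which is indexed at first prescription.

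**4. Odds models.** With no stated window, the odds of a recorded outcome depend on how long each patient is observed. As an illustration, assume no true effect and leaving rates of 8%/year (treated) against 10%/year (control). The observed risk over 15 years is h/(h+c) × (1 − exp(−15(h+c))), with c the leaving rate. For h = 0.005/year this is 4.24% against 3.78%, an odds ratio of 1.13. Across h = 0.002 to 0.01/year it is 1.126 to 1.131. Cox under independent censoring would give a hazard ratio of 1.

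**The case against.** The authors acknowledge the limitation. They say that IV survival methods are immature and plan to explore them secondarily. A risk difference is the natural output of an additive structural mean model, using methods with different approaches is deliberate, and the direction of effect stays comparable across scales. The Covariates section claims only partial control of unmeasured confounding. All of this stands, and it limits the point to the size of a disagreement. It does not remove the point, because the secondary survival models fix no measure or horizon that would make the results comparable.

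A reader might infer more: that a patient who leaves or dies before a window closes is counted as free of the outcome, so that groups with shorter follow-up look protected. The article does not say this. It gives no rule for incomplete windows, and a condensed article may leave that rule to the full plan. The size is also uncertain. With no true effect, a hazard of 1%/year and maximum follow-up of 6 against 15 years, such coding would give 48-month risks of 2.62% and 3.40% against a true 3.92%, a ratio of 0.77. But the Covariates section lists year of index date among the matching variables, which would shrink such a gap. Bias in an IV estimate also requires follow-up to differ by prescriber preference, which nothing shows. With leaving rates of 8% against 10%/year, the false 48-month difference is 0.25 to 1.23 per 1,000 for hazards of 0.002 to 0.01/year.

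Two further inferences go too far: that agreement or disagreement between methods cannot be interpreted at all, and that the cohort A index date must move. That date was chosen to limit immortal time bias, and moving it is a separate design question.

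**Conclusion.** The point holds for cohorts A and B as one of comparability. As written, the protocol's main IV result and its Cox result target different quantities over different periods, so the size of a difference between them cannot be assigned to confounding. How much of the information lies beyond the IV horizon depends on inputs the protocol does not give; under the assumptions above, 53% to 84% of observed events would come after 48 months. The IV part does not touch cohort C. The odds-ratio part reaches all three cohorts. Nothing here shows that the IV estimates would be biased by censoring; the protocol simply needs to say how incomplete follow-up is handled once windows are fixed.

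**What to change.** - Add longer IV horizons, for example 5 and 10 years. At each, include only patients whose index date allows that much potential follow-up, weight for loss to follow-up by inverse probability of censoring, and state a rule for death. The shorter windows may stay as secondary results.
- Report standardised risk differences from the Cox and propensity-matched analyses at the same horizons as the IV analysis, and base the comparison of methods on those.
- Give the logistic and odds models the same fixed horizons, or fit them as pooled logistic models on person-time.
- For cohort A, note when presenting the early windows that they may close before treatment; the index date stays as it is.

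The cost is protocol wording and programming on the same data. Fewer patients qualify at long horizons, so intervals there will be wider.

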#### Marginal structural models

In our fourth analysis, we will estimate the effects of each treatment using marginal structural models.^32^ We will use these models to account for time-dependent confounding and treatment switching. We will construct inverse probability weights for each treatment based on the patients' observed characteristics such as gender, age, comorbidities and concurrent treatments. We will use these models to estimate the odds and HRs of disease incidence and progression.

## Dissemination

We will publish the results of the study as open-access peer-reviewed publications. We will disseminate findings through national and international conferences as are appropriate. Depending on the findings, we would also explore additional options for focussed dissemination within appropriate communities, for example, via an Alzheimer's Society dissemination grant.
